# Autism Spectrum Social Stories In Schools Trial 2 (ASSSIST2): study protocol for a randomised controlled trial analysing clinical and cost-effectiveness of Social Stories™ in primary schools

**DOI:** 10.1186/s40359-020-00427-z

**Published:** 2020-06-12

**Keywords:** Social stories, Autism Spectrum conditions, School based interventions, Child mental health, Education

## Abstract

**Background:**

Interventions designed to support children with a diagnosis of Autism Spectrum Conditions (ASC) can be time consuming, needing involvement of outside experts. Social Stories™ are a highly personalised intervention aiming to give children with ASC social information or describing an otherwise difficult situation or skill. This can be delivered daily by staff in education settings. Studies examining Social Story™ use have yielded mostly positive results but have largely been single case studies with a lack of randomised controlled trials (RCTs). Despite this numerous schools are utilising Social Stories™, and a fully powered RCT is timely.

**Methods:**

A multi-site pragmatic cluster RCT comparing care as usual with Social Stories™ and care as usual. This study will recruit 278 participants (aged 4–11) with a clinical diagnosis of ASC, currently attending primary school in the North of England. Approximately 278 school based staff will be recruited to provide school based information about participating children with approximately 140 recruited to deliver the intervention. The study will be cluster randomised by school. Potential participants will be screened for eligibility prior to giving informed consent. Follow up data will be collected at 6 weeks and 6 months post randomisation and will assess changes in participants’ social responsiveness, goal based outcomes, social and emotional health. The primary outcome measure is the Social Responsiveness Scale Second Edition (SRS-2) completed by school based staff at 6 months. Approvals have been obtained from the University of York’s Research Governance Committee, Research Ethics Committee and the Health Research Authority. Study results will be submitted for publication in peer-reviewed journals and disseminated to participating families, educational staff, local authority representatives, community groups and Patient and Participant Involvement representatives. Suggestions will be made to NICE about treatment evidence dependent on findings.

**Discussion:**

This study addresses a much used but currently under researched intervention and results will inform school based support for primary school children with a diagnosis of ASC.

**Trial registration:**

The trial is registered on the ISRCTN registry (registration number: ISRCTN11634810). The trial was retrospectively registered on 23rd April 2019.

## Background

Autism Spectrum Disorders, often termed Autism Spectrum Conditions (ASC) [1] affects at least 1% of children in the UK [2]. ASC is a lifelong neurodevelopmental condition that can impact upon a range of child and adult outcomes [3, 4]. Children with ASC have a range of difficulties with social communication, sensory processing differences, and may have repetitive behaviours [5] and/or preoccupations [6]. They experience a higher prevalence of mental health problems than typically developing children including anxiety and low mood [7]. Many children with ASC struggle to manage social anxiety and feelings of frustration, which can lead to challenging behaviour [8–10]. Research shows that many people with ASC have additional care needs, both in the NHS and social care across childhood and adulthood [11, 12].

Social norms and classroom expectations can be difficult for children with ASC to learn and understand [13] and teachers facing many demands on their time and with limited training opportunities, may struggle to support their education [14].

[name]’s Social Stories™ are short, highly individualised stories that provide children with social information. They help children with ASC more easily understand a situation personal to them such as learning life skills, new experiences, understanding emotions (or people), transitions or change. The child is included in the narrative often with a range of helpful visual information. They are child friendly and do not require extensive involvement from outside experts [15]. Social Stories™ are defined by ten criteria that guide story development [16]. These help to ensure stories remain patient and supportive in tone using relevant, tailored content that is descriptive, meaningful, and safe for the child. The capacity for tailoring these stories is particularly important for helping children with ASC across a range of ages, strengths, difficulties and needs [17, 18]. Previous research examining Social Story™ use in specialist and mainstream education [19, 20] and within the home [18] shows largely positive results [21], and suggests that Social Stories™ may promote calmer classrooms with improved learning and better integration in Special Educational Needs (SEN) [19] and mainstream settings [20]. Children with ASC have shown improvements in social interactions [22–24], decision making [23], self awareness in communication [24] and mealtime skills [25]. Success has also been reported in reducing tantrums [26, 27] and managing frustration [28]. This research also suggests that it is possible to train tier one professionals, for example teachers, to develop and use Social Stories™ tailored to a child [29].

Despite this research, two systematic reviews of their effectiveness [30, 31] indicate large gaps in the literature. The reviews mainly identify single case designs and a lack of randomised controlled trial evidence.

This research is needed now because numerous schools utilise Social Stories™ despite a limited evidence base. This is highly relevant when many providers face limited resources for children with neurodevelopmental problems and mental health problems. Given that specialist practitioner interventions are in short supply, interventions such as Social Stories™ deserve robust evaluation as they can be delivered within schools on a day to day basis. We will be exploring these aspects within our study. This study follows an RCT that assessed the feasibility and acceptability of running a trial examining Social Story™ use in both primary and secondary mainstream schools [32]. This demonstrated a high degree of acceptability with young people, family and schools. This main trial now seeks to assess the clinical and cost-effectiveness of Social Stories™, addressing the lack of fully powered RCTs in this area.

### Study aim

To assess the clinical and cost-effectiveness of Social Stories™ alongside care as usual in primary schools when compared with care as usual alone.

### Study objectives

#### Primary

The primary objective of the study is to establish whether Social Stories™ can improve social responsiveness in children with ASC in primary schools across Yorkshire and the Humber, when compared to children who have received care as usual only.

#### Secondary

The secondary objectives of this trial are:
To investigate whether Social Stories™ can reduce challenging behaviour in children with ASC in primary schools.To investigate whether Social Stories™ can improve social and emotional health in children with ASC in primary schools.To assess the cost-effectiveness of Social Stories™.To examine the effects of Social Stories™ delivered in the classroom on general measures of health related quality of life.To examine whether Social Stories™ improve classroom attendance.To assess sustainability of Social Stories™ in an education setting across a 6 month period.To examine any changes in parental stress.To examine any associations between treatment preference and outcomes.To examine how elements of session delivery (e.g. session frequency, length and any associated problems/adverse events) are associated with outcomes.

### Trial design

This trial is a multi-site pragmatic cluster RCT comparing Social Stories™ and care as usual with a control group receiving care as usual alone. Care as usual is defined as the existing support routinely provided for a child with ASC from educational and health services such as specialist autism teacher teams, mental health teams or other associated professionals. The trial includes a 10 month internal pilot, a process evaluation (including qualitative interviews and an examination of treatment fidelity) and an economic evaluation.

## Methods

### Study setting

Participants will be recruited using a variety of methods including identification through schools, or identification through participating NHS trusts using their clinic lists/databases. Intervention delivery will take place in the participant’s school.

### Eligibility criteria

Both the school and the child’s parents/guardians must agree to take part before either may be included. Eligibility to take part will be ascertained using the following criteria.

Inclusion criteria:
The child is aged 4–11 years.The child attends a participating primary school within Yorkshire and the Humber.The child has a clinical diagnosis of ASC and daily challenging behaviour.Parents/guardians of the child are able to self-complete the English language outcome measures (with assistance if necessary).

Exclusion criteria:
The school has used Social Stories™ for any pupil in the current or preceding school term.The child or interventionist teacher has taken part in the previous Social Stories™ feasibility study (ASSSIST). Schools that have taken part will not be excluded.

### Intervention

Children in the intervention arm of the trial will receive the Social Stories™ intervention in addition to their care as usual.

The Social Stories™ intervention will be delivered by a trained educational professional (the interventionist) who is employed within each school allocated to the intervention arm. The interventionist may vary between the schools (e.g. a teacher, teaching assistant (TA), or Special Educational Needs Coordinator (SENCO)). Social Stories™ used within the trial will be based on a goal developed mainly by an education professional who knows the participating child well but is not the interventionist (the associated teacher). This goal will be developed with support from the study team; and where possible the parent/guardian, interventionist and the child. A Social Story™ is used to provide a child with social information and works well if a child is uncertain or finds a situation distressing, frustrating or incomprehensible.

Interventionists will be trained by the research team or through trained local authority autism specialist staff. Training will include information on the design and implementation of Social Stories™, with materials based on those developed in the preceding feasibility study with the support of [name] [32] and a Social Stories™ manual produced by the study’s Chief Investigator (CI) and a Clinical Psychologist with expertise in autism [33]. During the training session, interventionists will construct a Social Story™. Parents/guardians will also be invited to attend these sessions. Following training all Social Stories™ will be assessed against a fidelity checklist, to ensure they conform to the ten established criteria [16, 33]. They will then be delivered to children in the intervention arm by the interventionist at least six times over a 4 week period.

Goal based outcome measures will be used and 20 % of children allocated to the intervention arm will be observed by a blinded research assistant to ascertain their progress towards the goal. Consent to these observations will be optional and participants will be randomly selected by the Trials Unit using a computer generated list from those who have opted in.

### Control

Participants allocated to the control arm of the trial will receive care as usual. Schools in the control arm are asked to refrain from delivering any Social Stories™ for the duration of their trial involvement.

If a participant decides to withdraw from the intervention and/or the study, a member of the research team will record details including reasons provided, whether withdrawal is from the whole study or an individual element, and whether they wish to continue providing data for analysis.

### Outcomes (primary and secondary)

Baseline and follow-up measures will be collected during visits to schools, participants’ homes or at locations convenient to participants or via post where face to face data collection is not possible. The primary outcome is the Social Responsiveness Scale, Second Edition (SRS-2) [34] completed at 6 months post-randomisation by the associated teacher. The SRS-2 measures social interaction skills and ASC symptomatology.

All secondary outcomes are listed below (grouped by respondent) and will be collected at baseline, 6 weeks and 6 months post-randomisation unless specified. The trial flow chart is seen in Fig. 1.

**Fig. 1 Fig1:**
[figure not shown]
Study Flow Chart

Parent questionnaires:
Social Responsiveness Scale, Second Edition (SRS-2) [34].Demographic information pertaining to the child and the parent – *baseline only.*Parenting Stress Index short form [35].The EQ-5D-Y (proxy) [36].Revised Children Anxiety and Depression Scale (RCADS) short form [37].Bespoke resource use questionnaire, capturing healthcare and non-health resource use of participants and parents/carers– *baseline and 6 months only.*Bespoke treatment preference questionnaire – *baseline only.*

Associated teacher/TA questionnaires:
Social Responsiveness Scale, Second Edition (SRS-2) [34].A goal-based outcome measure (adapted from the Child Outcomes Research Consortium) [38].Bespoke resource use questionnaire – *baseline and 6 months only.*Bespoke treatment preference questionnaire – *baseline only.*Bespoke resource use questionnaire determining current school care/education plan interventions – *baseline and 6 months only.*

Interventionist Teacher/ TA Questionnaires:
Bespoke Social Story™ session log. – *used after each Social Story™ session.*A bespoke sustainability questionnaire – *6 weeks and 6 months only.*

Process Evaluation - Researcher Questionnaires:
A fidelity checklist (intervention arm only) assessing each Social Story™ - *after the story has been created and at 6 weeks post-randomisation*.A goal-based measure – used when observing randomised children at 6 weeks and 6 months.

### Sample size calculation

The primary outcome is the teacher completed SRS-2 t-score at 6 months. Within the pilot data, outcomes were measured at 6 and 16 weeks. The correlation between baseline and 6 weeks (*r* = 0.67, 95% CI 0.44 to 0.80) was lower than that at 16 weeks (*r* = 0.83, 95% CI 0.68 to 0.91) for the pilot data. To be conservative we have chosen the lower 95% confidence limit for the lowest correlation between baseline and follow-up that we observed within our pilot data (*r* = 0.44). Assuming a difference of 3 points, SD = 7, 5% alpha, 90% power, average cluster size 1.35, ICC = 0.34, correlation = 0.44 and 25% attrition requires a total sample size of 278.

### Recruitment

The study aims to recruit 278 children with ASC from across Yorkshire and the Humber. Recruitment opened in November 2018. In addition, the study will recruit 278 parents/guardians, 278 associated teachers and approximately 140 interventionists who will each complete study questionnaires, and in the case of interventionists, deliver Social Stories™ sessions.

ASSSIST2 will use five methods of participant recruitment outlined in more detail below:

#### Recruitment from schools

Primary schools across Yorkshire and the Humber will be contacted with information about the trial. Where schools agree to participate they will be asked to send information sheets and Expression of Interest (EOI) forms to parents/guardians of eligible children. Parents/guardians who return an EOI form or have consented for school staff to pass on their details will be contacted by a member of the research team to discuss the trial, answer any questions and to arrange collection of informed consent from parents/guardians and where possible assent from the child. We will also gain consent from education professionals taking part in the trial.

#### Recruitment from NHS sites

Participating NHS Trusts who carry out autism spectrum assessments will be asked to identify potentially eligible families through screening of their clinic/database lists. A member of the clinic team (or delegated staff member) will send study information and EOI forms to the child’s parent/guardian. Recruitment will then follow the procedure set out for schools.

#### Recruitment from local community groups

Local community groups within the catchment area, e.g. the Autism Spectrum Conditions - Enhancing Nurture and Development (ASCEND) parent group [39], will be contacted with information about the trial and researchers will distribute study information to interested parents/guardians. On receipt of an EOI, recruitment will follow the procedure outlined for schools.

#### Liaising with local authority professionals

Relevant local authority professionals, e.g. educational specialists in ASC, will be contacted and asked to disseminate study information and EOI forms to the parents/guardians of potentially eligible children. On receipt of an EOI recruitment will follow the procedure outlined for schools.

#### Recruitment from local publicity

Families may hear about the trial from a range of sources and contact the research team. In this instance the team will confirm the child’s eligibility and send out study information. It will be made clear that participation is dependent on the child’s school taking part and recruitment will continue in line with the procedure outlined for schools.

### Randomisation

Randomisation will occur after consent/assent and baseline data has been obtained from all participating families and educational professionals within a school. Remote randomisation for the trial will be carried out by the York Trials Unit (YTU). Schools will be randomised using cluster randomisation to reduce the risk of contamination within schools with multiple participating children. Randomisation will be stratified by school type (SEN school or mainstream school) and by the number of participating children within a school (≤5 or > 5 participating children).

Following randomisation schools will be notified of study allocation via phone call, email and following letter. Participating parents/guardians will receive a confirmatory letter.

### Blinding

Research assistants collecting outcome data and the main trial statistician will be blinded to study allocation until final data analysis. It is not possible for children, parents/guardians or school staff to be blinded to study allocation due to the nature of the intervention. The Data Monitoring and Ethics Committee (DMEC) will have access to un-blinded data throughout the study. Any instances of un-blinding will be recorded using a bespoke form. In such instances a substitute blinded research assistant will collect participant data wherever possible.

### Data collection

Data collection will utilise paper Case Report Forms (CRFs). To maintain participant confidentiality CRFs will be anonymised using participant ID numbers. Data collection will occur at baseline, 6 weeks and 6 months post-randomisation. Wherever possible baseline CRFs will be completed in person and where not possible, participants will be offered the option to return them by post.

### Data management

All information collected during the study will be kept strictly confidential and stored on a secure password protected server located at the University of York, for the purposes of assisting in follow-ups during the study. All paper documents will be stored securely.

CRFs will be initially checked for errors by the research team and any queries raised immediately with participants. CRFs will then be logged on the YTUs bespoke data management system and scanned using Cardiff Teleform. Original datasheets will be securely stored at YTU. All data will be collected and retained in accordance with the Data Protection Act 2018, the General Data Protection Regulation 2018 and YTU standard operating procedures (SOPs). All data will be archived for 10 years following the end of the study and then securely destroyed.

### Statistical analysis

Statistical analyses will be conducted using a validated statistical software package and will be reported in line with the Consolidated Standards of Reporting Trials (CONSORT) 2010 Statement [40]. The primary analysis population will be intention to treat (ITT).

#### Primary and secondary outcomes analysis

The primary analysis will compare teacher reported SRS-2 t-scores measured at 6 months between the randomised groups using a covariance pattern mixed model. Important baseline covariates, baseline SRS-2 t-score, the SEN status of the child’s school (SEN vs. non-SEN), the number of recruited children in the child’s school (> 5 vs. ≤5), time point, treatment group, and a treatment group-by-time point interaction will be included as fixed effects and school will be included as a random effect. SRS-2 t-scores at 6 weeks post randomisation will be incorporated as outcome data. The model will account for the correlation of scores within pupil over time by means of an appropriate covariance structure. Intervention effects in the form of an adjusted mean difference will be presented with an associated 95% CI and *p*-value for both time points (6 weeks and 6 months).

Secondary outcomes will be analysed in a similar manner to the primary analysis, adjusting for the appropriate baseline score being tested. The summary of Adverse Events (AEs) and Serious Adverse Events (SAEs) experienced by participants will be reported by treatment group.

Subgroup analyses will be performed to explore the potential effect of teacher’s preferred randomisation group collected at baseline. The primary analysis model will be refitted with an interaction term between the randomisation group and teacher’s preference. A Complier Average Causal Effect analysis for the primary outcome will be considered to account for compliance with the intervention at the student level.

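### The primary repeated-measures model gives baseline SRS-2 one slope for both follow-up visits; a baseline-by-time term would cheaply remove a small bias that arises only if baseline-dependent dropout differs between arms

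*Protocol article*

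**What the plan says.** The section on primary and secondary outcomes analysis in the protocol article specifies a covariance pattern mixed model for the teacher-completed SRS-2 t-score. Both follow-up visits are outcomes: "SRS-2 t-scores at 6 weeks post randomisation will be incorporated as outcome data". The list of fixed effects opens with "Important baseline covariates, baseline SRS-2 t-score, the SEN status of the child’s school (SEN vs. non-SEN", continues with the number of recruited children in the school, and ends "time point, treatment group, and a treatment group-by-time point interaction will be included as fixed effects". School is a random effect. Within-pupil correlation is handled "by means of an appropriate covariance structure". Treatment-by-time is the only interaction listed. Secondary outcomes are to be analysed in a similar way, each with its own baseline score.

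The sample size section reports two pilot correlations with baseline. The earlier one is introduced as follows: "The correlation between baseline and 6 weeks (*r* = 0.67, 95% CI 0.44 to 0.80) was lower". The later one, from the 16-week visit, is 0.83 with a 95% interval running from 0.68 up to 0.91. The section gives no pilot correlation for 6 months. For sizing it takes 0.44, the lower confidence limit of the 6-week correlation, as a conservative choice. With the other inputs, "25% attrition requires a total sample size of 278".

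**The concern.** A baseline main effect in a two-visit model is one regression slope shared by 6 weeks and 6 months. The trial's own pilot suggests the slopes may differ, since the 6-week correlation "was lower than that at 16 weeks". If they do, the shared slope lies between them, and part of the baseline score stays unadjusted at 6 months, the primary time point.

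In complete data, randomisation balances that remainder between arms. With missing 6-month scores, balance can be lost if the children who remain differ in baseline severity between arms. Dropout that depends only on observed baseline and arm is missing at random, and a likelihood-based mixed model with the right mean structure handles it. Here it might not, because one term is absent.

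The condition is conceivable. Families and school staff know the allocation, school staff supply the primary outcome, and 25% attrition is planned for. The article does not say that dropout will depend on baseline or differ by arm.

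**Working it through.** **1. Sample size (reproduces).** Inputs from the sample size section: difference 3, SD 7, 5% alpha (taken as two-sided), 90% power, cluster size 1.35, ICC 0.34, correlation 0.44, attrition 25%.
- n per arm = 2 × (7 × (1.960 + 1.282) / 3)² = 114.4
- × (1 − 0.44²) = 92.3
- × design effect (1 + 0.35 × 0.34 = 1.119) = 103.2
- ÷ 0.75 = 137.7 per arm, or 275.3 in total; rounding up at each step gives 280.

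The stated 278 lies between these and is not in dispute.

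**2. How far apart the pilot correlations are.** On the Fisher z scale, atanh(0.83) − atanh(0.67) = 1.188 − 0.811 = 0.377. Standard errors read from the stated intervals are 0.160 and 0.178. Then z = 0.377 / √(0.160² + 0.178²) = 1.58, p = 0.11. This treats the two correlations as independent. They are not if the same children were measured at both visits, so it is only indicative.

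**3. Assumptions for steps 4 to 6.** Equal SDs at all visits, so that slope equals correlation. The 16-week value 0.83 stands in for 6 months. Unstructured within-pupil covariance, residual between-visit correlation ρ from 0.3 to 0.7, complete 6-week scores, 1:1 allocation, clustering handled by the design effect.

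**4. Precision with complete data.** In SD units the residual variances are 1 − 0.67² = 0.551 (6 weeks) and 1 − 0.83² = 0.311 (6 months), with residual SDs s₁ = 0.742 and s₂ = 0.558. Under generalised least squares the shared slope weights the 6-week slope by s₂² − ρs₁s₂ and the 6-month slope by s₁² − ρs₁s₂.
- ρ = 0.3: weights 0.187 and 0.427; shared slope 0.67 + 0.16 × 0.696 = 0.781
- ρ = 0.5: weights 0.104 and 0.344; shared slope 0.793
- ρ = 0.7: weights 0.021 and 0.261; shared slope 0.818

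The proportional variance loss at 6 months is (0.83 − shared slope)² / 0.311. This is 0.76%, 0.44% and 0.05%, or 0.4%, 0.2% and 0.02% of the standard error. The shared slope sits near the 6-month slope because that visit has the smaller residual variance.

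**5. Precision with 25% missing at 6 months.** In 2,000 simulated trials per setting (effective n = 278 / 1.119), with dropout odds ratio 2 per baseline SD in one or both arms and ρ of 0.3 or 0.5, the standard error rose by 0.4% to 1.1%. The standard error itself was about 0.56. A rough check that ignores borrowing from 6 weeks: 278 × 0.75 / 1.119 / 2 = 93.2 per arm, and 7 × √0.311 × √(2 / 93.2) = 0.57.

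**6. Bias at 6 months.** Both models were fitted by maximum likelihood to 400,000 simulated children, with true effect −3 and 25% missing at 6 months by a logistic model on baseline. Bias is in T-score points, and its sign depends on which arm loses the more severe children.

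| Dropout dependence on baseline | One shared slope | With baseline-by-time |
|---|---|---|
| None, or the same in both arms | 0.02 or less | 0.02 or less |
| One arm only, odds ratio 2 per SD | 0.09 to 0.12 | 0.01 or less |
| Opposite directions, odds ratio 2 | 0.20 to 0.24 | 0.01 or less |
| Opposite directions, odds ratio 3 | 0.29 to 0.33 | 0.01 or less |

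A hand check supports the second and third rows. Let b be the shared slope under dropout (0.772 at ρ = 0.5), let κ = ρs₂/s₁ = 0.5 × 0.558 / 0.742 = 0.376, and let Δ be the arm difference in completers' mean baseline in SDs. Then bias ≈ 7 × Δ × [(0.83 − b) + κ(b − 0.67)]. The bracket is 0.058 + 0.376 × 0.102 = 0.096. With 25% dropout at odds ratio 2 per SD, integrating the logistic model over a normal baseline puts completers 0.159 SD from the full-sample mean.
- One arm only: 7 × 0.159 × 0.096 = 0.11
- Opposite directions: 7 × 0.318 × 0.096 = 0.21
- Same in both arms: Δ = 0, so bias is 0

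**7. Sensitivity.** If the 6-week slope were at its lower limit, 0.44, with 0.83 at 6 months, the odds-ratio-2 biases would be 0.15 to 0.19 (one arm) and about 0.37 (opposite directions). The standard error cost would be 2% to 3%.

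**The case against.** The case for leaving the model alone has real force. A single baseline slope is a conventional choice and contradicts nothing in the article. The pilot intervals overlap, the later pilot visit is 16 weeks, and correlations translate to slopes only if the SDs at the visits are alike, which the article does not report. A bias of 0.1 is small beside a standard error of 0.56. The article condenses a fuller protocol, and the SAP is not shown and may already contain the term. All of this stands and sets the weight low. It does not remove the point, because the article lists the fixed effects explicitly and the list imposes the restriction.

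Three stronger readings are tempting, and the document supports none of them.
- A reader might infer that baseline-dependent dropout is enough to cause bias. It is not: the slope misfit cancels when the dependence is alike in both arms.
- A reader might take 0.44 as the expected 6-month correlation and conclude that correlation falls sharply after 6 weeks. The article presents 0.44 as the lower limit of the 6-week estimate, used as a sizing margin, and the pilot point estimates rise with time. Losses or biases computed with 0.44 at 6 months have no basis.
- A reader might infer a material loss of power. With complete data, power falls by 0.2 percentage points or less, and if the true correlation is nearer the pilot values the trial has precision to spare.

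**Conclusion.** The point holds in a limited form. As written, the primary model ties the 6-week and 6-month baseline slopes together, and nothing in the article supports that restriction. At the pilot values it costs about 1% of the standard error or less, and there is no bias under dropout that is alike in both arms. If dropout depends on baseline differently in the two arms, the 6-month effect is biased by roughly 0.1 to 0.2 points, or 3% to 7% of the 3-point target (0.1/3 and 0.2/3) and about 0.2 to 0.4 standard errors (0.1/0.56 and 0.2/0.56). Reaching 0.3 needs strong dependence in opposite directions.

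These sizes rest on equal SDs across visits, the 16-week correlation standing in for 6 months, and an assumed dropout mechanism that the article neither states nor predicts. The sample size of 278 is unaffected. Severity is low; the case for acting is that the safeguard costs almost nothing.

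**What to change.** Add a baseline SRS-2 t-score-by-time point interaction to the fixed effects of the primary model, and keep the 6-month group difference from that model as the primary estimate. Add the matching baseline-by-time term to each secondary outcome modelled over both visits. If the SAP already includes these terms, no change is needed beyond confirming it.

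The cost is one extra parameter per model and one sentence of analysis text, settled before allocation is unblinded. No additional data or children are required.
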